### 2.4. Participants

Participants will be selected from the databases of the Department of Developmental Neuroscience of the IRCCS Stella Maris (Pisa, Italy) and of the Azienda USL Toscana Nord Ovest (Italy). Eligible subjects and their families will subsequently receive invitations to participate in the study, and informed consent will be obtained from either the subjects and/or their caregivers before the enrolment. Subjects will be recruited according to the following specific inclusion criteria:Congenital or acquired developmental disabilities;Age between 6 and 30 years at the time of recruitment;Cognitive functioning that allows sufficient understanding of proposed activities and cooperation in exercises investigated by appropriate rating scales (Wechsler Preschool and Primary Scale of Intelligence (WPPSI)-III, WPPSI-IV [37], Wechsler Intelligence Scale for Children (WISC)-IV [38], Wechsler Adult Intelligence Scale (WAIS)-IV [39], Leiter International Performance Scale—Revised Edition [40], Leiter International Performance Scale—Third Edition [41], Color progressive [42] or Standard progressive Raven matrices [43]);Distance from the clinical center that allows periodic in-person evaluation of progress;Internet access at home;Caregivers able to be committed to and cooperate in an intensive rehabilitation home-based program;Manual Ability Classification System (MACS) [44] level < V;Subjects will be excluded in case of severe comorbidities (such as behavioral impairments, auditory and visual impairments) and/or severe cognitive disability that may preclude adequate cooperation in clinical assessment and during the tele-rehabilitation sessions.

As mentioned above, after the enrolment, participants will be stratified according to several criteria, including (i) diagnosis (congenital or acquired developmental disorder group), (ii) GMFCS level (GMFCS I-II/GMFCS III–IV), (iii) age (6–10/11–15/16–20/21–30), (iv) and technology utilized (APP vs. Home Kit). Randomization, sequence generation and preparation of group allocation materials will be carried out by an independent researcher who will not be involved in the trial. Using a computer-generated set of random numbers, they will be then allocated to experimental or control groups. Participants, parents, and clinical staff will be aware of the allocation group. Pairs will be randomly divided into two groups with a 1:1 experimental/SC (wait-list) ratio. Participants assigned to the experimental group will begin treatment with technology immediately for a 3-month period, while those in the SC group will continue with their usual care.

### 2.5. Study Procedure and Intervention

Subjects meeting the eligibility criteria will be directed to the research team for enrolment. All the comprehensive details about the study procedures will be provided to participants and/or their caregivers during an interview before obtaining informed consent. Thus, demographic and clinical measures will be collected. Beyond detailed assessment and procedures planned for the study will be conducted at IRCCS Stella Maris Foundation and Azienda USL Nord-Ovest.

For the study purposes, two different technologies will be implemented for the pediatric population and used for cognitive, motor, and language tele-rehabilitation: the VRRS Home Kit Tablet and the MedicoAmico APP. Since VRRS is one of the several home-based technologies available and has shown promising results in previous studies involving pediatric patients for various rehabilitation purposes, including speech and motor therapy [33,34], we decided to use this technology in this study.

#### 2.5.1. VRRS Home Kit Tablet

VRRS features a wide range of innovative non-immersive virtual reality medical devices, incorporating a multi-domain technology developed by Khymeia (an Italian Small–Medium Enterprise, SME) and tested for rehabilitation both in clinical settings and tele-rehabilitation. Utilizing biofeedback and augmented feedback mechanisms, VRRS enhances user engagement and compliance [45,46]. Initially designed for the adult population, recent applications with children and adolescents have shown promising preliminary outcomes [32,34,47,48].

Among different VRRS devices, VRRS Home Kit Tablet (Figure 5a) allows cognitive, language and motor rehabilitation to be delivered at home through tele-rehabilitation pathways. This system encompasses a tablet with a wide exercise library and different USB peripheral devices, such as balances and sensors (K-sensors, i.e., inertial measurement unit (IMU) sensors; K-wand) supporting motor rehabilitation across different body districts (i.e., upper and lower limbs, trunk). Moreover, touch screen activities enable neuropsychological and speech therapy sessions.

Considering that the VRRS Home Kit Tablet is currently mainly used for adulthood rehabilitation, during the project the library of exercises will be reviewed and re-organized, selecting those most suitable for the pediatric population, also considering the functional profile of different neurodevelopmental disabilities. Furthermore, activities will be enriched with options to customize the exercises’ difficulties, including self-progression of levels, duration, speed and amplitude of movement, with new scenarios to enhance engagement and interactivity for children.

#### 2.5.2. MedicoAmico APP

MedicoAmico APP (Figure 5b) is a medical device for tele-medicine and tele-rehabilitation, developed by Khymeia, downloadable on patients’ smartphones or tablets following General Data Protection Regulation (GDPR). The app comprises a library of cognitive, language and motor exercises that will be implemented during the project. Indeed, new packages of modular interactive exercises will be developed, featuring parameters including duration, repetitions, difficulty, speed, pace and amplitude of movement. The new exercises will include images and specific instructions tailored for children and adolescents, followed by a post-activity self-assessment rating.

Specifically, within the motor library (Figure 6a), new exercises will be created to address the rehabilitation of global coordination, gross motor skills, and functional balance. These activities will include imitating movements performed by a robot-like avatar and searching materials to build motor paths guided by auditory and/or visual cues.

Concerning the speech and cognitive library (Figure 6b), current exercises will be reviewed and categorized based on neuropsychological processes (i.e., attention, visuospatial and verbal working memory, inhibition) and language skills (i.e., lexical and semantic skills, reading and writing skills) involved. Furthermore, the exercises will be modified to be more suitable for pediatric use, arranging additional settings and enabling a progression of increasing difficulty in line with self-advancement criteria. Within these libraries, activities most suitable for each subject will be identified, facilitating the development of customized treatment protocols.

#### 2.5.3. Treatment Procedure

The designated devices for tele-rehabilitation (VRRS Home Kit or MedicoAmico APP) will be delivered to participants’ homes. Moreover, a dedicated printed manual with instructions will be provided, also including all the contacts of both technical and clinical staff for remote assistance in case any problems occur during the treatment. This will follow a familiarization phase with clinicians explaining the system’s operating procedures to participants and their caregivers, including safety aspects.

The treatment will last for 3 months, with a frequency of about 2–3 sessions per week, according to the rehabilitation goals and users’ needs. Clinicians will consistently monitor the progression of the treatment using a dedicated web platform. The sessions would be performed in two modalities: (i) online, with clinicians interacting in real-time with the patient, also having the remote control of the system; (ii) offline, with the patient executing alone the training session before scheduled by clinicians.

During the initial period, clinicians will supervise the treatment online, guiding both patients and their families in system utilization. As patients and caregivers become more confident in using the system and according to treatment goals, online sessions will be decreased in favor of offline ones.

### 2.6. Outcome Measures

#### 2.6.1. Primary Outcome Measures

The acceptability and usability of ICT technologies in pediatric populations will also be assessed through the following Key Performance Indicators (KPIs), summarized in Table S1.

Service and technology KPIs:Study adherence: rate of acceptance of the participation in the study calculated as the number of eligible participants that agree to join the project;Adherence to training: total number of training sessions completed on the total number of sessions scheduled by the clinicians;Number of dropouts: number of participants that will not complete all of the study procedures;Number of sessions completed in the target time: total number of training sessions completed in the timeframe set by clinicians;Hardware and software technical problems: number of issues and malfunctioning experiments during the training sessions;Ad hoc feasibility questionnaires: according to the standard definitions of usability [49,50,51] and acceptability [52], specific items ranked on a five-point Likert scale (1 most negative, 5 most positive) will be defined. The aim will be to investigate four feasibility domains: (i) exercise customization, (ii) adaptability of home training, (iii) required effort and (iv) systems suitability. An introductory section will include both open and multiple-choice questions to collect information about the patient, the experimenter who fills out the questionnaire, and the devices and peripherals used. Three questionnaire versions will be available for different stakeholders (participants, parents, clinicians). The children’s format will be structured to be easy to understand for even the youngest participant and facial expressions shown through emoticons will help the children to assign the Likert-scale rank. Questionnaires will, therefore, be filled out at the end of the training by clinicians who administered the session, parents and participants over 6 years old and with cognitive and neuropsychological functioning, allowing full question comprehension and adequate cooperation;Medical Equipment Utilization: for each involved technology: the average time of utilization per session; the related consumables (if any)—the related power consumption;Set-up time: the time necessary for setting up the involved technologies;Training time/learning curve (for patients).

Operational KPIs related to the impact of tele-rehab on facilities’ performances (inpatient–outpatient and at-home rehab services):Average length of hospital-facility stays: self-explanatory;Patient wait time for the first rehabilitation session;Bed turnover: number of discharges in the given time period/number of beds in the facilities during that time period;Bed occupancy rate: number of occupied beds on the total beds;Readmission rate: total readmissions on the total number of patients;Number of patients treated: self-explanatory;Number of beds dedicated: self-explanatory;Staff to patient ratio: number of staff needed per patient per session;Space requirements (in square meters) of the facilities’ surface requested for the specific treatments;Training time/learning curve (for healthcare professionals or families) in supporting patients during the rehab sessions;Physiotherapists’ mental workload: the amount and complexity of information decisions physiotherapists have to manage or make per session.

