Within this framework, TABLET TOSCANA aims to develop innovative organizational models that foster the continuity of care through tele-rehabilitation for neuro-psychomotor and language functions using Khymeia technological devices in subjects with congenital and acquired developmental disabilities. Particularly, organizational dimensions, acceptability, the usability of proposed solutions, and the performance of the involved ICT, unrelated to the effectiveness of tele-rehabilitation, will be assessed as the primary objective of the study, differently from traditional literature. In addition, the secondary objective will be to evaluate the clinical effectiveness of the tele-rehabilitation intervention. We hypothesize that the TABLET TOSCANA project could establish a new organizational model to be implemented at the territorial level and integrated into routine clinical practice, improving the taking charge of the rehabilitation services for children with neurodevelopmental disabilities.

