#### 2.1.2. Phase II

During this phase, the validation of the implemented technologies will be conducted through a wait-list study (Figure 3) with two parallel arms. One hundred subjects (comprising 80 children and 20 young adults) will be recruited from the aforementioned clinical centers. The wait-list design study will ensure that all enrolled patients will be eligible for the experimental treatment, thus avoiding issues related to equipoise.

After the identification of eligible subjects according to inclusion and exclusion criteria (described below), participants will be stratified according to several criteria, including (i) diagnosis (congenital or acquired developmental disorder group), (ii) gross motor function classification system (GMFCS) level (GMFCS I–II/GMFCS III–IV), (iii) age group (6–10/11–15/16–20/21–30), (iv) and technology utilized (APP vs. Home Kit). Then, participants will be randomly assigned to the experimental group (EG)—receiving a 3-month tele-rehabilitation immediately—or the wait-list group (WG)—continuing traditional rehabilitation care for the same duration. All subjects will be evaluated before (T0) and after (T1) the 3-month intervention period (tele-rehabilitation or traditional rehabilitation), using standardized clinical tests. Moreover, participants enrolled in the WG will be re-evaluated at the end of the 3 months of tele-rehabilitation training (T1 plus). Finally, at the end of tele-rehabilitation training, ad-hoc questionnaires will be administered to the main stakeholders to assess the systems’ usability and acceptability. The program of enrolment, interventions and assessments designed according to SPIRIT guidelines are shown in Figure 4.

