### 2.7. Statistical Analyses

Descriptive statistics (means, standard deviation, frequencies) will be investigated, analyzing potential baseline differences between groups explored and computing the p values. The normal distribution of the sample will be investigated through the Shapiro–Wilk test. Subsequently, a comprehensive analysis, both qualitatively and quantitatively, will be conducted on the questionnaire data gathered from various stakeholders, aiming to assess the usability and acceptability of the devices used. Statistical analysis, such as ANOVA or regression, will be carried out to determine differences based on age, diagnosis, functional profile (cognitive and motor outcomes), and devices used during tele-rehabilitation. Furthermore, inferential analyses will be carried out to assess pre–post-treatment differences, gain efficacy data, and also consider the different devices used during tele-rehabilitation pathways. Finally, flowchart diagrams will be created to illustrate the different organizational models identified. Statistical significance will be considered at p<.05. Statistical Package for Social Sciences (SPSS) (IBM Statistic) will be adopted for carrying out the statistical analyses.

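### The usability and acceptability questionnaires have one stated time point, the end of the 3-month training, and none at early stopping, so the scores are likely to be too favourable

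*Protocol article*

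**What the plan says.** The Introduction places organisational dimensions, acceptability, usability and technology performance at the centre of the trial; these "will be assessed as the primary objective of the study, differently from traditional literature". Clinical effectiveness is secondary.

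Among the primary outcome measures in Section 2.6.1 are ad hoc feasibility questionnaires, for which "specific items ranked on a five-point Likert scale (1 most negative, 5 most positive) will be defined". They cover four domains: customisation of exercises, adaptability of home training, effort required and suitability of the system. Participants, parents and clinicians each have their own version.

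The timing is stated twice. Section 2.6.1: "Questionnaires will, therefore, be filled out at the end of the training by clinicians who administered the session, parents and participants". Section 2.1.2: "at the end of tele-rehabilitation training, ad-hoc questionnaires will be administered to the main stakeholders". Section 2.5.3 sets the training at 3 months. No interim form and no form at withdrawal is described.

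The same primary list also counts giving up. One entry is "Number of dropouts: number of participants that will not complete all of the study procedures", another is "Adherence to training: total number of training sessions completed on the total number of sessions scheduled by the clinicians", and a third counts technical problems during sessions.

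Section 2.7 then uses the questionnaire data for comparisons: "Statistical analysis, such as ANOVA or regression, will be carried out to determine differences based on age", and also on diagnosis, functional profile and device.

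**The concern.** A family that stops before the 3 months are over has no stated occasion to rate the system. Three of the four domains (effort, adaptability at home, suitability) are also plausible reasons for stopping. Whether a rating is obtained would then depend on what the rating would have been, and the ratings obtained would lean towards the satisfied.

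The loss occurs at collection, so no later analysis plan can make it good: a rating never asked for cannot be recovered. It also bears on comparisons. If one device or age group loses more people than another, the group with more losses has its score raised more, and a real difference can shrink or vanish. According to Section 2.1.3, the results are meant to define organisational models for the Regional Health Service.

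**Working it through.** **Plan's own figure.** There is none to reproduce. The article gives no expected dropout rate, no acceptability threshold and no expected score. Only the 1–5 scale, the time point and the 3-month duration come from the document. Everything numerical below is an assumption, shown over a range.

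**Formula.** Let p be the share of starters who stop early and are not surveyed, C the mean score of completers and S the mean score that stoppers would have given. The reported mean is C. The mean over all starters is (1 − p)·C + p·S. The difference is

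C − [(1 − p)·C + p·S] = p·(C − S),

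that is, dropout share times score gap.

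**Mean score.** Overstatement in Likert points:

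| Dropout p | Gap 0 | Gap 1 | Gap 2 |
|---|---|---|---|
| 5% | 0 | 0.05 | 0.10 |
| 10% | 0 | 0.10 | 0.20 |
| 20% | 0 | 0.20 | 0.40 |
| 30% | 0 | 0.30 | 0.60 |

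For example, with p = 0.20, C = 4.0 and S = 3.0, the mean over all starters is 0.8 × 4.0 + 0.2 × 3.0 = 3.8, against a reported 4.0.

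**Share of favourable ratings.** Assume that 80% of completers and 20% of stoppers rate favourably. The share among all starters is (1 − p) × 80 + p × 20, which gives 77%, 74%, 68% and 62% at 5%, 10%, 20% and 30% dropout. The reported figure is 80% each time.

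**Device comparison.** Assume that 80% of completers and 30% of stoppers rate favourably on either device, and that one device loses 10% of its users and the other 30%.

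- First device: 0.9 × 80 + 0.1 × 30 = 75%.
- Second device: 0.7 × 80 + 0.3 × 30 = 65%.

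Both would be reported as 80%. A difference of 10 percentage points among starters disappears from the questionnaire result, although it would leave a trace in the dropout counts.

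**What the other indicators supply.** Dropout and adherence give p. They do not give S, nor the domain in which the system failed, so p·(C − S) cannot be worked out from them. Technical problems are logged during sessions, but effort and suitability are not. The patient and parent interviews in Section 2.1.3 concern unmet needs along the care pathway; they do not provide the Likert ratings, and the text does not say whether stoppers are included.

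**The case against.** The strongest reply is that the article does not exclude early stoppers. The end of training can be read as the end of each person's own training. Section 2.1.2 plans an evaluation of all subjects after the 3-month period, so contact with stoppers may be possible. Section 2.7 defines no completers-only analysis set. A condensed article may also leave withdrawal procedures to the full protocol. This stands as a limit on how firmly the point can be put. It does not remove the point: the timing is stated twice and tied to the end of a fixed 3-month programme, and the planned evaluation of all subjects is described in terms of clinical tests. If the individual reading is intended, one sentence settles it.

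Three stronger readings are tempting, and the documents do not support them.

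- A reader might infer that people who give up go unmeasured. They do not: dropouts, completed over scheduled sessions, sessions completed in the target time and technical problems are all in the same primary set. Poor feasibility would show there. Only the questionnaire component is exposed.
- A reader might infer that acceptability is certainly overstated. That requires stoppers to go unsurveyed and to rate lower. Stops for unrelated reasons need not carry a low rating, and with no gap there is no bias.
- A reader might infer that clinicians' repeated ratings will be analysed as independent. Section 2.7 names its methods only as examples, and the form records who fills it out, so a clinician term can be fitted. A simple design effect also does not carry over in general to patient-level contrasts that vary within clinician.

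**Conclusion.** The point holds for the questionnaire component of the primary outcome set. With one stated time point at the end of training and none at stopping, the plan as written would draw its ratings mainly from completers, and those ratings are likely to be too favourable. The size is the dropout share times the completer–stopper gap: 0.05–0.60 points for 5–30% dropout and a gap of 1–2 points, and nothing if the gap is zero. Both inputs are assumed. Confidence is therefore high about what the text says and moderate at best about the size. Distortion of device, age or diagnosis comparisons further requires dropout, or the gap, to differ between the groups compared. The change is still worth making, because the missing information cannot be recovered afterwards and the form already exists.

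**What to change.** Add one sentence to Section 2.6.1: anyone who starts tele-rehabilitation and stops early, together with their parent and treating clinician, completes the same questionnaire at the time of stopping. The existing eligibility condition on the participant's comprehension can stay.

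Report questionnaire scores with the number of responders out of all starters, by device, next to the dropout and adherence indicators. For stoppers who do not respond, add a sensitivity analysis over a range of assumed scores. The lowest category is the worst case, not the expected value, since not every stop reflects dissatisfaction.

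The cost is an existing form sent at a second time point. Some stoppers' forms will be missing, and others will reflect short exposure, so time in training should be shown with them. The Data Availability statement says that enrolment was in progress, and wait-list participants begin tele-rehabilitation only after T1, so the change could still reach participants who had not yet finished training when the article was written.

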### 2.3. Sample Size

Based on the annual count of children referred to the recruiting centers for clinical management and rehabilitation, a final sample of 100 subjects is deemed sufficient for conducting a *t*-test to analyze differences in primary endpoints between groups, assuming an effect size (d) of at least 0.4, a significance level (α) of 0.05, and a power (1-β) of 0.8.

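### Bed turnover and bed occupancy, and readmission rate on its likelier reading, are primary KPIs on facility totals, so they mix treated and untreated patients and have no value per randomized arm

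*Protocol article*

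**What the plan says.** The Introduction makes organizational dimensions part of the primary objective. Section 2.6.1 (Primary Outcome Measures) accordingly includes a list of operational KPIs, headed as the impact of tele-rehabilitation on how the facilities perform. Three matter here:

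- "Bed occupancy rate: number of occupied beds on the total beds".
- Bed turnover: discharges in a period divided by the beds in the facilities in that period.
- "Readmission rate: total readmissions on the total number of patients".

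None of these lines is limited to trial participants or to an arm.

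On the design, section 2.1.2 says "One hundred subjects (comprising 80 children and 20 young adults) will be recruited from the aforementioned clinical centers". Section 2.4 adds "Pairs will be randomly divided into two groups with a 1:1 experimental/SC (wait-list) ratio". The experimental group is described as "receiving a 3-month tele-rehabilitation immediately", while the wait-list group continues usual care and has its own 3 months of tele-rehabilitation after T1. Both arms are drawn from the same two centres.

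Section 2.3 justifies the sample for "conducting a *t*-test to analyze differences in primary endpoints between groups". The inputs are a standardized difference of 0.4 or more, α = 0.05 and 80% power. It makes no exception for the operational KPIs.

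**The concern.** The unit that is randomized and treated is the individual, but the unit these KPIs describe is the facility. Two consequences follow.

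1. Bed occupancy or bed turnover in a centre that treats both arms is one number. There is no experimental-arm occupancy and no wait-list occupancy, so randomization gives these KPIs no comparison.
2. If the facility figure is instead read over time, most of what moves it may come from patients who never received tele-rehabilitation, together with case mix, season and bed policy.

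Section 2.1.3 says the results will define organizational models for the planning of the Regional Health Service. A flat or drifting bed figure listed as a primary outcome could then be taken as evidence about tele-rehabilitation when it carries little information on it.

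**Working it through.** **The plan's own figure.** Section 2.3 gives 100 subjects for a between-group t-test with d = 0.4, α = 0.05 and power 0.8. The usual formula per arm is n = 2(z₀.₉₇₅ + z₀.₈)²/d² = 2(1.960 + 0.842)²/0.16 ≈ 98. With the t correction it is about 99, or 198 in total. The figure of 100 does not reproduce: 50 per arm gives about 51% power two-sided. That is a separate matter. What counts here is that the stated test needs one value per participant in each arm.

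**Step 1: does each KPI have a value per arm?**

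| KPI | Denominator as written | Value per arm? |
|---|---|---|
| Bed turnover | beds in the facilities | no |
| Bed occupancy | total beds | no |
| Readmission rate | total number of patients, not said whose | no if the facilities' patients; yes if participants counted by arm |
| Staff ratio, mental workload | per session | not a facility total |
| Space | per specific treatment | not a facility total |

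This step uses only the text and needs no assumed volume.

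**Step 2: how many are on tele-rehabilitation at once?** With 100 subjects, 1:1 allocation and consecutive 3-month blocks, simultaneous enrolment puts 50 on treatment at a time. With staggered recruitment and the same blocks, the simulated average peak is about 52 to 56 when recruitment takes 3 to 6 months, 32 when it takes 12 months and 20 when it takes 24 months. About half is therefore a fair upper figure on average.

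**Step 3: dilution.** Let F be the number of patients counted. F is not in the documents and is assumed. If the rate is p₀ in the untreated and p₁ in the treated, then

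facility rate = p₀(1 − 50/F) + p₁(50/F).

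Take an assumed p₀ = 20% and p₁ = 10%. The drop in percentage points is then 10 × 50/F.

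| F (assumed) | Treated share | Facility rate | Drop (points) |
|---|---|---|---|
| 100 | 50% | 15.0% | 5.0 |
| 200 | 25% | 17.5% | 2.5 |
| 500 | 10% | 19.0% | 1.0 |
| 1000 | 5% | 19.5% | 0.5 |
| 5000 | 1% | 19.9% | 0.1 |

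F = 100 is the limiting case in which the facilities treat nobody but the trial subjects; even then half are untreated.

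**Step 4: power.** Two periods of F patients each were compared at the facility level, with readmission halved in the treated from an assumed 10%, 20% or 30%. Power never exceeds 22% over F = 100 to 5000. An undiluted comparison of 50 against 50 participants has about 16%, 29% and 43% respectively. Counting participants therefore removes the dilution and restores the randomized comparison, but does not make the trial well powered for readmission.

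**The case against.** The best case for the plan has five parts.

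- **The readmission line does not name its population.** Bed turnover refers expressly to the facilities; readmission does not. Section 2.6.2 says outcomes are collected through eCRFs that record, among other things, the performances of the involved children, which is compatible with a trial-patient denominator. This stands. The heading favours the facility reading, and other KPIs in section 2.6.1 say participants where trial subjects are meant, but the text does not settle it. If the count is within each arm, readmission is neither diluted nor unsplittable.
- **Detail may lie elsewhere.** Table S1 and the full protocol are not shown. This stands for time windows and comparators. It does not remove the point for the bed KPIs, whose denominators this document states.
- **Facility volume is unknown.** A reader might infer that an effect cannot show at all. The documents do not support that: the size of the dilution depends on an unstated number, and the counted unit could be a small dedicated service. A reader might also rescale d = 0.4 by the treated share. For a single facility ratio with no patient-level standard deviation, that has no clear meaning.
- **No passage makes a bed figure decisive.** Section 2.1.3 draws on usability, acceptability, feasibility and efficacy data, interviews and focus groups, and section 2.7 names no test on bed KPIs. This tempers the consequence. Section 2.3 nevertheless speaks of primary endpoints without exception, and these KPIs are listed among them.
- **Facility performance is the declared object.** Counting participants answers a somewhat different question. That is true, and it is why the bed figures should be kept as context and not deleted.

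**Conclusion.** The point holds for bed turnover and bed occupancy, and for readmission rate if it counts the facilities' patients. These primary KPIs mix experimental, wait-list and non-trial patients and have no value per arm, so the between-group comparison in section 2.3 cannot be made on them. That conclusion follows from the text alone.

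Dilution is the second, weaker ground. Its direction is certain whenever non-treated patients are counted. Its size rests on assumed facility volumes and readmission rates: on those assumptions, a 10-point drop in the treated becomes 2.5 points at 200 patients and 0.1 at 5000. Effects are then unlikely to be visible, which is different from impossible. Participants may also contribute few bed-days, since section 2.4 does not require an inpatient stay and treatment is given at home.

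A reader might extend the point to the whole operational list. That would be wrong: staff ratio, space and mental workload are defined per session or per treatment and are not affected.

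**What to change.** - State whose patients form the denominator of the readmission rate.
- Define readmissions and inpatient or facility days per enrolled participant over T0–T1, and compare them by randomized arm.
- Keep bed turnover, bed occupancy and number of beds as descriptive context for the centres. State that they are outside the between-group test and are not used to judge the effect of tele-rehabilitation.
- Do not compare the wait to first session by arm, because allocation itself sets when tele-rehabilitation starts.
- Leave the per-session and per-treatment KPIs as they are.

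The cost is a change of KPI wording and a few extra eCRF fields per participant. Events will be few and intervals wide, so the results should be reported as estimates with intervals, and a non-significant result should not be read as no effect.
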